### Estimands

To provide full clarity for our first two objectives, the corresponding estimands are described in Table 1.

**Table 1 Tab1:** Structured statement of estimands

	**Total effect**	**Overall effect**
Description	Effect of offering vaccination to clusters in 1–30-year-olds who would take it	Effect of offering vaccination to clusters in 1–30-year-olds
Target population (to whom the treatment effect applies)	Residents of Vellore aged 1–30 years who would take their assigned treatment	Residents of Vellore aged 1–30 years
Treatment condition (including the population exposed to an offer)	TyphiBEV® vaccination of those aged 1–30 years, including catch-up for late recruits (but not for participants who move from a control to a vaccination cluster)	Offer of TyphiBEV® vaccination to those aged 1–30 years, including catch-up for late recruits (but not for participants who move from a control to a vaccination cluster)
Endpoint	Blood culture-confirmed typhoid fever within 2 years	Blood culture-confirmed typhoid fever within 2 years
Summary measure/s	Marginal individual average incidence rate ratio	Marginal individual average incidence rate ratio
Intercurrent event handling	Refusal of vaccine offer by participants in vaccine clusters will be handled using a principal stratum strategy (which is our interpretation of the total effect), as will taking of vaccine by participants in non-vaccine clusters	Refusal of vaccine will be handled using a treatment policy strategy (which corresponds to the overall effect)
	**Migration**	**Migration**
	*Out of the study area* will be handled by censoring the participant at the point they leave	*Out of the study area* will be handled by censoring the participant at the point they leave
	*Into study area* will be treated as late recruitment	*Into study area* will be treated as late recruitment
	*From control cluster to control cluster* does not affect the estimand	*From control cluster to control cluster* does not affect the estimand
	*From vaccine cluster to vaccine cluster* does not affect the estimand	*From vaccine cluster to vaccine cluster* does not affect the estimand
	*From vaccine cluster to control cluster* will be censored	*From vaccine cluster to control cluster* will be censored
	*From control cluster to vaccine cluster* will be censored	*From control cluster to vaccine cluster* will be censored

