### Statistical analysis

Our primary summary measure of the effect is a rate ratio (RR), from which vaccine effectiveness can be expressed as (1 − RR) × 100%. This will be estimated using an individual-level analysis using Poisson regression that will account for time at risk with censoring at the last known follow-up time. This is expected to be less than 2 years when participants migrate out of the study area. We will present an adjusted RR from a regression model including, covariates, the randomisation strata, participant age, gender, and household size. We will also compute unadjusted RRs but the adjusted RR will be considered ‘primary’. A difference in rates will also be computed after fitting the regression model, by standardization [13]. We will present both measures with 95% confidence intervals and two-sided hypothesis tests that consider a *p*-value of < 0.05 to be significant. Inference will be based on the bootstrap for the total effect and will use robust standard errors to account for clustering for the overall effect.

For measures of vaccine effectiveness which are described here as contrasts between vaccinated participants in vaccine clusters and unvaccinated participants in non-vaccine clusters, such as the total effect, we will use instrumental variable methods. Under this approach, while data from all participants are included in the analysis, we estimate the effect of vaccine only in those who would take it if available in their cluster (i.e. would ‘comply’). Although we do not observe this compliance in the non-vaccine arm, by randomisation we would expect the same proportion as in the vaccine arm, and this underlies the approach. The details of exactly how this will be done will be specified in subsequent versions of the statistical analysis plan.

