The time at risk for the overall effect will begin 28 days after vaccination is completed in all intervention clusters. For participants that move into a trial cluster from outside the trial area, time at risk for the overall effect will begin at recruitment. For the total effect, time at risk for non-vaccine clusters begins as for the overall effect. In vaccine clusters, this will begin 28 days after vaccination is completed across clusters or 28 days after an individual is vaccinated (whichever is later) and no risk-time is contributed by those unvaccinated. Time at risk ends at the study’s close, the time of an event (culture-confirmed typhoid fever), withdrawal from the study, or migration from the study area or within the area but between trial arms (whichever is earliest).

The primary outcome might have missing data if a trial participant with a febrile illness visits a study-associated healthcare facility but refuses a blood culture. We will describe the frequency of such refusals by trial arm. We will multiply impute the blood culture results for these participants under the missing at random assumption and conduct sensitivity analyses to explore the impact on the total and overall vaccine effect estimates of making alternative assumptions.

We do not have any plans for interim analyses of vaccine effectiveness, or subgroup analyses except that we will estimate the total effect in participants aged 1–14 years. We will conduct simple descriptive analyses of safety events in vaccinated participants, and of vaccine uptake in eligible vaccine arm participants.

A first draft of a detailed statistical analysis plan has been created and will be finalised before analysis.

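### The risk-time rule for the primary total effect leaves out unvaccinated people in vaccine clusters, which contradicts the instrumental-variable analysis of all participants and the principal-stratum estimand

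*Protocol article*

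**What the plan says.** Three parts of the protocol article bear on how unvaccinated people in vaccine clusters enter the primary analysis.

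- **Estimands, Table 1, total effect.** The target population is those who would take their assigned treatment. "Refusal of vaccine offer by participants in vaccine clusters will be handled using a principal stratum strategy".
- **Statistical analysis, estimation method.** The general model is an "individual-level analysis using Poisson regression that will account for time at risk". For contrasts "such as the total effect, we will use instrumental variable methods". Under that approach, "while data from all participants are included in the analysis, we estimate the effect of vaccine only in those who would take it". Compliance is not observed in non-vaccine clusters, but "by randomisation we would expect the same proportion as in the vaccine arm, and this underlies the approach". The exact implementation is left to a later statistical analysis plan.
- **Statistical analysis, time at risk.** "For the total effect, time at risk for non-vaccine clusters begins as for the overall effect". In vaccine clusters it starts at the later of two dates: 28 days after vaccination is complete across clusters, or 28 days after the person's own vaccination. There, "no risk-time is contributed by those unvaccinated".

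The Vaccination section keeps refusers and ineligible people under fever surveillance, so their outcomes will be recorded.

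**The concern.** In a rate model, a person with no risk-time adds neither events nor denominator. The risk-time rule therefore removes the outcome data of every unvaccinated person in the vaccine clusters, whereas the method paragraph says everyone's data are used.

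The removed data are what the described method needs. Takers and non-takers cannot be told apart in control clusters. An IV analysis separates them by borrowing the non-takers' rate from the vaccine clusters, where they can be identified. Without that rate, and with no restriction on controls, the contrast is takers against a mixture of would-be takers and non-takers.

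Non-takers are not only refusers. The Vaccination section also withholds vaccine from people with a typhoid vaccine in the past 3 years and from pregnant or nursing women, among others. Equal baseline risk cannot be presumed.

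At stake is whether the primary estimate keeps the protection of randomisation. Two incompatible specifications also leave room to choose between them once data are seen.

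**Working it through.** **Inputs from the Sample size calculation section.** Lowest assumed uptake p = 0.75; risk reduction 70% (rate ratio 0.30); control incidence 190 per 100,000 per year; 60 clusters of about 2800, hence 30 per arm; 47% of the population under 30; 2 years.

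**Assumed, not in the documents.** r = baseline typhoid rate of non-takers divided by that of takers, from 0.5 to 2. d = indirect protection of non-takers in vaccine clusters, 0, 10% or 30%.

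**The plan's own figure.** The protocol gives no figure for this bias. Its related figure, power above 90%, comes from a simulation whose details are in an additional file that is not shown, so it cannot be reproduced. An approximate cluster-trial rate formula (30 clusters per arm, 1316 participants each, between-cluster coefficient of variation k assumed) gives, at k = 0.5, 95.4% power for the overall effect and 99.9% for the total effect. At k = 0.75 the figures are 81.3% and 97.9%. The stated power is plausible and is not disputed here.

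**Step 1: what the rule removes.** Take 2800 as the whole cluster population, with 47% eligible, and r = 1 without indirect protection.

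- Participants per arm: 30 × 2800 × 0.47 = 39,480.
- Removed from vaccine clusters: 39,480 × 0.25 = 9,870 people; × 2 years = 19,740 person-years; × 0.0019 = about 38 events.
- Removed from control clusters: none. All 39,480 people count, with 39,480 × 2 × 0.0019 = about 150 events.

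**Step 2: expected VE if the risk-time rule governs.** Let the takers' baseline rate be 1. The control rate is p + (1 − p)r and the vaccinees' rate is 0.30, so

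VE = 1 − 0.30 / (0.75 + 0.25r).

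At r = 2: 1 − 0.30/1.25 = 76.0%. At r = 0.5: 1 − 0.30/0.875 = 65.7%.

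**Step 3: expected VE if the non-takers are kept in an IV analysis.** The takers' control rate is recovered as

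[(0.75 + 0.25r) − 0.25r(1 − d)] / 0.75, and VE = 1 − 0.30 / that rate.

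At r = 2, d = 0: (1.25 − 0.50)/0.75 = 1.00, VE 70.0%. At r = 1, d = 30%: (1 − 0.175)/0.75 = 1.10, VE 72.7%.

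| r | Vaccinees vs all controls | IV, d = 0 | IV, d = 10% | IV, d = 30% |
|---|---|---|---|---|
| 0.5 | 65.7% | 70.0% | 70.5% | 71.4% |
| 1 | 70.0% | 70.0% | 71.0% | 72.7% |
| 1.5 | 73.3% | 70.0% | 71.4% | 73.9% |
| 2 | 76.0% | 70.0% | 71.9% | 75.0% |

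**Step 4: the start of the clock.** Reading completion as the end of the initial round, anyone vaccinated in that round was vaccinated on or before that date. The later-of-two rule therefore gives them the common date, as in control clusters. The arms differ for in-migrants: in control clusters their time starts at recruitment, in vaccine clusters 28 days after their own vaccination. An illness soon after recruitment would count in one arm only.

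**The case against.** The strongest defence is that the protocol commits to IV methods and a principal stratum and leaves the implementation to the analysis plan. That deferral covers how the IV analysis is done. It does not cover risk-time, which the article fixes, so the conflict stands.

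A reader might infer that the primary estimand cannot be computed. The documents do not support that. Uptake is counted among participants, not derived from person-time, so it stays known. Some principal-stratum estimators model compliance in the vaccine arm and weight the controls by it, without non-takers' outcomes. They need an added assumption of no unmeasured confounding of compliance and outcome, and the article rests its approach on randomisation instead. So the estimand could be reached under the rule, but not by the route described.

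A reader might also infer that the clock differs between arms for everyone. It does not; see Step 4.

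Restoring the risk-time is also not a clean cure. Indirect protection of non-takers is one of the trial's exploratory objectives, and it would violate the exclusion restriction on which a standard IV estimate depends. At r = 1 with 30% indirect protection, the IV estimate is 72.7%, while the criticised contrast is exactly 70%. This objection stands and shapes the fix.

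Finally, the bias depends on an unknown r, is zero at r = 1, and may shrink after adjustment for strata, age, gender and household size. All of that stands.

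**Conclusion.** The contradiction is real and concerns the primary analysis: the risk-time rule cannot describe the same rate analysis as the IV paragraph and Table 1. Which one governs is not stated, so the documents do not support saying that the trial will report a per-protocol contrast. They support saying that it would if the risk-time rule is followed.

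In that case, at 75% uptake and a true VE of 70%, the expected estimate moves by about −4 to +6 percentage points for r from 0.5 to 2, before covariate adjustment. Wider ranges based on lower uptake would fall below the protocol's own floor and are not used. A shift of this size would not threaten a superiority conclusion. It would affect the VE estimate and any claim that effectiveness exceeds a margin, which the sample size section mentions.

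**What to change.** Reconcile Table 1, the IV paragraph and the time-at-risk paragraph before the analysis plan is finalised.

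1. State that in the IV or principal-stratum analysis of the total effect, unvaccinated vaccine-cluster participants contribute events and person-time from the common start date, and that vaccination status enters only through the compliance model.
2. Keep the vaccinated-only risk-time rule for a sensitivity analysis labelled as per-protocol.
3. State the assumption that allocation has no effect on non-takers, and add a sensitivity analysis over a range of indirect protection.
4. For late recruits only, start risk-time by the same rule in both arms, without reference to the person's own vaccination date.

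Items 1, 2 and 4 are mainly wording; item 3 adds a small analysis. No new data are needed, because the unvaccinated remain under surveillance. At submission, clusters had not been randomised and the analysis plan was a first draft.

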### Data management, confidentiality, and quality assurance (QA)

Operational management of the trial will be aided by an externally validated, custom-built database management software. It will link with the VDSS and be used for recruitment, scheduling, and tracking of participant contacts and outcomes. Primary clinical data will be recorded on validated instances of Redcap (Research Electronic Data Capture) [14, 15] software forms, hosted on hybrid cloud servers within India, with built-in range and value checks. A dedicated data management team will generate regular data queries and backups. Access to the custom software and Redcap forms will be password protected and conducted via pre-approved tablets or laptop computers. Activities such as data entry, backup, validation, and export will be conducted as per SOPs and appropriately logged.

We will consider any document where demographic, clinical, or laboratory data is first recorded prior to entry into our digital Case Record Forms (CRFs) as source data. This includes hospital records, clinical charts, office charts, pharmacy, and laboratory records. If hospital data is unavailable in electronic format, the study team will maintain scanned copies until the CRFs are verified. If a CRF is the first place where data is entered, it will be considered source data. Hardcopy study documents will be stored securely in a confidential location. To maintain the anonymity of participants, they will only be referred to by their participant ID on study documents, except in informed consent sheets. All data collected during the trial will be stored at the site for at least 3 years after its completion. The PI will have complete access to the final dataset.

A dedicated QA team will regularly validate a proportion of the data entered into CRFs and ensure that all trial processes follow the protocol and Good Clinical Practices. The microbiology labs that process blood samples will participate in an external QA programme. The study processes will be reviewed by an external monitoring team at the end of one year.

### Trial oversight

A Trial Steering Group (TSG), comprised of the lead investigators, the data manager, internal quality manager, and the trial statisticians, will meet at least once a month to discuss trial operations. Interim reports will be prepared for the independent Data Safety and Monitoring Board (DSMB), comprised of an epidemiologist, statistician, paediatrician, physician, and a clinical pharmacologist, to address the recruitment of participants, vaccine uptake, and event rates in both arms of the trial. The DSMB will review these data to decide whether any additional sample size calculations are required, and whether to recommend an extension of the trial to allow more outcome events to accumulate. The board will advise the TSG on changes that may be required in the trial’s operations to achieve its objectives.

A Scientific Advisory Group, comprised of the lead investigators, independent experts in clinical trials and community interventions, representatives from the Directorate of Public Health, and policy experts, will also review the processes and progress of the trial once every 6 months and provide feedback.

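### The DSMB may use event rates in both arms to recommend an extension while the final test stays at an unadjusted 0.05, so that level is not shown to be protected if the trial is extended

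*Protocol article*

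**What the plan says.** Three statements in the protocol article bear on this.

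- **Trial oversight.** Interim reports go to the DSMB "to address the recruitment of participants, vaccine uptake, and event rates in both arms of the trial". The next sentence gives their use: "The DSMB will review these data to decide whether any additional sample size calculations are required", and also "whether to recommend an extension of the trial to allow more outcome events to accumulate". No trigger, timing or maximum length is given, and nothing limits the decision to data pooled over arms.
- **Statistical analysis, on interim looks.** "We do not have any plans for interim analyses of vaccine effectiveness".
- **Statistical analysis, on the final test.** "We will present both measures with 95% confidence intervals and two-sided hypothesis tests", taking a p-value "value of < 0.05 to be significant". No adjustment is mentioned for a duration chosen during the trial.

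Other sections treat the duration as fixed. Fever surveillance ends the trial 25 months after vaccination, and the endpoint in Table 1 is typhoid within 2 years.

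**The concern.** The primary summary measure is a rate ratio. If the DSMB sees the typhoid rate in each arm, it sees that ratio's numerator and denominator, whether or not anyone fits a model or computes a p-value. Using those rates to decide how long to follow participants makes the final analysis time depend on the treatment contrast. A fixed 1.96 critical value then no longer guarantees a 5% false-positive rate, and a 95% interval no longer guarantees 95% coverage.

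The statement that no interim effectiveness analysis is planned would lead a reader to assume that this cannot happen. If the trial were extended, the sponsor would need evidence from outside the article that the extension did not depend on the effect. The result is meant to inform national decisions on vaccine roll-out, so that question would be asked.

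**Working it through.** **1. The stated figure.** One final test at a fixed time, rejecting when |Z| > 1.96, has level 2 × (1 − Φ(1.96)) = 0.050. The plan's 0.05 is correct for a fixed duration.

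**2. Model for an extension.** Measure information as a fraction of the planned total. Under the null, let B(s) be Brownian motion and Z(s) = B(s)/√s. The DSMB looks at fraction t. The trial then either ends at 1 or is extended to T, and is tested once at its actual end with 1.96. The true level is

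α = ∫ φ(z) · P(|Z(end)| > 1.96 given Z(t) = z) dz,

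where the end is T if the rule extends at z, and 1 otherwise. The article gives neither t nor T nor a rule. I assumed t = 0.5, 0.75 and 1.0, and T = 1.25, 1.5 and 2.0.

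**3. Results.** Each range runs over the three values of T.

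| Basis for extending | t = 0.5 | t = 0.75 | t = 1.0 (planned end) |
|---|---|---|---|
| Independent of the arm contrast, such as pooled counts | 5.0% | 5.0% | 5.0% |
| Result not significant (z between −1.96 and 1.96) | 5.3–5.8% | 5.6–6.4% | 7.1–8.3% |
| Absolute z between 1 and 1.96 | 4.6–4.9% | 5.1–5.2% | 7.0–7.4% |
| Conditional power 50–90% | 4.5–4.8% | 4.2–4.7% | not applicable |
| Worst-case extend-or-not rule | 5.5–6.2% | 5.8–6.8% | 7.1–8.3% |

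As an example, take t = 1, T = 2 and extension when the result is not significant. The level is P(|Z(1)| > 1.96) + P(|Z(1)| < 1.96 and |Z(2)| > 1.96) = 0.050 + 0.033 = 0.083.

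**4. Clustering.** Between-cluster differences that persist through an extension make the two looks more alike, which reduces the inflation. Take 150 events and 30 clusters per arm, with between-cluster CV k. The variance of the log rate ratio is 2/150 + 2k²/30 at the planned end and (2/150)/T + 2k²/30 after extension. The correlation of the two z values is the square root of the second variance over the first. For k = 0.5 and T = 1.25 this is √(0.02733/0.03000) = 0.954. The planned-end, not-significant rule then gives 6.4%. Over k = 0.25 to 0.5 and the same T values, the range is 6.4–7.9%. The article gives no k, so these values are assumed.

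**5. Can an event target be read off the article?** Its inputs give 30 × 2,800 × 0.47 = 39,480 eligible people per arm. If 190 per 100,000 applies at ages 1–30, two years give 39,480 × 2 × 0.0019 = 150 control events. With 75% uptake and 70% effect, the vaccine arm has 150 × (1 − 0.75 × 0.70) = 71, making 221 in all. This is not a usable target:

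- It is the count for the secondary overall effect. For the primary total effect, cases among the vaccinated are about 39,480 × 0.75 × 2 × 0.0019 × 0.30 = 34.
- It leaves out indirect protection.
- It does not correspond to a fixed power. With variance 1/150 + 1/71 + 2k²/30, overall-effect power is 0.999 at k = 0, 0.971 at k = 0.5 and 0.870 at k = 0.75.

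The claim of more than 90% power comes from a transmission simulation in Additional file 2, which is not shown. The stated power is plausible and is not in question here.

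**The case against.** Four points can be made for the plan.

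- **Purpose.** The article ties an extension to accumulating events, not to a difference between arms. A decision on event numbers leaves the level at 5.0%. The wording could also mean rates across both arms. This stands as a reason not to call inflation certain. But the data named for the decision are most naturally read as by arm, and nothing excludes their use.
- **No strict contradiction.** Monitoring reports to an independent board, with no modelled estimate, no test and no early stopping for efficacy, need not count as an effectiveness analysis. Both statements can be literally true, and repeated-testing inflation from early efficacy stopping does not arise. A decision informed by the contrast remains possible, so the two statements still need to be reconciled.
- **Unseen documents.** A trigger or cap may sit in the DSMB charter, the full protocol or the analysis plan. Their absence from an article is no fault. The point concerns what the article does state: which data inform the decision.
- **Advisory role.** The DSMB only recommends, and an extension may never happen. That is true and limits the practical risk.

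A reader might infer that type I error is bound to rise to 7–8%. The documents do not support that. Those figures need a significance test at the planned end followed by extension if it fails, and the article describes no such step; it speaks of interim reports. Nor does every extension on a promising result inflate error: several such rules at an interim look give 5% or less.

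**Conclusion.** The concern holds in a limited form. As written, by-arm event rates may inform the length of the trial, and the final test carries no protection for that, so the 0.05 level is not shown to hold after an extension. This falls short of showing that it fails.

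For a mid-trial decision, the plausible excess under a not-significant rule is about 0.3 to 1.4 percentage points (5.3–6.4%), and the worst binary rule reaches 6.8%. Only a decision at the planned end on the test result reaches 7.1–8.3%, or 6.4–7.9% with the assumed clustering. All these figures depend on assumed timing, extension length and rule. Deciding on pooled counts removes the issue. The correction is worth making because it is cheap and is best made before by-arm outcomes are reviewed; the article reports that clusters had not been randomised at submission.

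**What to change.** Change the Trial oversight sentence, and the DSMB charter to match, so that sample size recalculation and any extension are decided only on the pooled number of culture-confirmed cases and on uptake. Set in advance:

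- an event target taken from the sponsor's own power simulation, not from adding up the article's inputs;
- a maximum duration, with the 25-month end of surveillance and the 2-year endpoint in Table 1 reconciled to any extension.

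If the DSMB must see by-arm rates for other reasons, it should record the pooled decision first. If by-arm rates are meant to drive the decision, pre-specify the rule together with a final test that preserves alpha, such as a combination or conditional-error test, and amend the statement on interim analyses accordingly.

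The cost is one protocol sentence and a charter edit, with no extra data. The downside is small: under the pooled rule the DSMB cannot tailor an extension to the observed effect.
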